## Abstract

**Background:**

Asthma self-management (e.g., trigger avoidance or correct medication use) is a cornerstone of therapy. Its successful implementation in everyday working life is determined by psychosocial working conditions, in particular by support from superiors and colleagues and the job decision latitude (i.e., when and how to carry out which tasks). To empower individuals with asthma to modify their working conditions, employees need to use certain communication skills and acquire specific knowledge. Both could be taught as part of patient education during pulmonary rehabilitation. Therefore, the aim of the planned study is the development and multicentre implementation of an education module for individuals with asthma during their rehabilitation and to generate evidence on its effectiveness.

**Methods:**

Participants (*n* ≥ 180) will be recruited, randomized into an intervention and a control group, trained and surveyed in two rehabilitation clinics. The intervention group will receive the supplementary patient education module “Asthma and Work” while the control group will participate in a program on " Eating behaviour” (both 2 × 50 min). The effectiveness of the intervention will be examined based on pre-post measurements (T1 and T2) and a 3-month follow-up (T3). We will consider behavioural intention (T2) and asthma self-management at work (T3) as primary outcomes. Secondary outcomes will include self-management-related knowledge, self-efficacy, number of sick days, number of exacerbations, asthma control (Asthma Control Test), asthma-related quality of life (Marks Asthma Quality of Life Questionnaire), and subjective employment prognosis (Brief Scale Measuring the Subjective Prognosis of Gainful Employment). The pre-post comparisons are to be evaluated using univariate analyses of covariance.

**Discussion:**

Improving asthma self-management at work could increase the work ability and social participation of employees with asthma. This could reduce costs, e.g. in terms of asthma-related sick leave.

**Trial registration:**

German Clinical Trials Register (ID: DRKS00031843)

**Supplementary Information:**

The online version contains supplementary material available at 10.1186/s12890-024-02847-8.

## Background

Self-management of asthma (e.g., trigger avoidance, respiratory physiotherapy techniques for shortness of breath or irritable cough, correct application of medication based on a written therapy and emergency plan, and communication about the disease) is an important component of therapy [1–3]. Qualitative and quantitative findings suggest that beneficial psychosocial working conditions are associated with better asthma self-management at work [4, 5], but also with improved asthma control, asthma-related quality of life, and the subjective employment prognosis (including the personal assessment of the ability to continue working until retirement age, the risk to earning capacity and the intention to apply for a pension) [6, 7]. Among the psychosocial working conditions relevant to asthma self-management, social support (from colleagues and superiors) [4, 5] and decision latitude at work (i.e., the extent to which work tasks and working hours can be determined at one’s own discretion) represent key factors [4]. Communication skills and comprehensive education about relevant patient and employee rights may enable patients to improve these psychosocial working conditions– and thereby, among other things, their asthma self-management [4].

Patient education in the context of pulmonary rehabilitation could be an important approach to empower patients with asthma to modify their workplace in a self-determined manner with consideration of their condition [8]. This endeavour could be understood in terms of the concept of “job crafting”, which assumes that employees can proactively redesign their work situation [9, 10]. It thus implies that an individualized, bottom-up approach to job redesign is possible, as opposed to top-down approaches and organization-initiated “one-size-fits-all” solutions [9, 11, 12]. Even employees in presumably rigid work environments and low-autonomy workplaces appear to have the ability to make some changes to their work demands and resources [9].

In Germany, individuals with asthma mostly receive inpatient pulmonary rehabilitation (duration: about three weeks). Currently, rehabilitation clinics in Germany often schedule only 15 min for patient education on the topic “asthma at work” - along with the complex topics “coming out as an asthmatic” and “asthma in the family” [13]. The aim of the planned multicentre intervention study is to develop and implement a novel patient education module addressing “Asthma and Work” in more depth in pulmonary rehabilitation. The effectiveness of the module will be examined in a randomized controlled trial (RCT) with a follow-up period of 3 months.

In the new patient education module, a change in working conditions is to be achieved by initially increasing knowledge and raising awareness of the topic [3]. However, research has shown that the increased knowledge alone does not translate into behavioural change among patients, but that there are factors that mediate the translation of knowledge into behaviour [14]. Therefore, based on the Theory of Planned Behaviour (TPB), [15–17] we assume that the intention to actually perform a certain behaviour (hereafter referred to as “behavioural intention”) is the most proximal precursor of the behaviour itself (here: asthma self-management at work). An important determinant of the behavioural intention is, in turn, an individual’s confidence in having sufficient skills and in one’s abilities to perform a given behaviour [15, 18, 19]. In the TPB, this concept is referred to as perceived behavioural control and is based on Bandura’s self-efficacy theory [20]. Therefore, in addition to knowledge transfer, we aim to increase job-related self-efficacy, defined here as the confidence that patients feel able to implement their own desired self-management strategies at work, through social skills training (e.g., role-play).

We hypothesise that the behavioural intention related to the implementation of appropriate asthma self-management will improve at the end of the rehabilitation program (T2). As mentioned above, the behavioural intention is considered a key determinant of successful asthma self-management at work [15, 20]. Then, after 3 months and the possible return to work (T3), actual asthma self-management at work should have improved due to prior proactive initiation of changes of relevant individual working conditions. Thus, behavioural intention will be used as primary outcome at T2 while asthma self-management will serve as primary outcome at T3. Self-management-related knowledge and self-efficacy along with other factors (see below) will represent the secondary outcomes. The potential improvement in asthma self-management at work and related improvement in asthma control, asthma-related quality of life, and the subjective employment prognosis (see above) [6, 7] could then reduce the number of exacerbations and sick days (and also related costs). Therefore, we will also examine asthma control, asthma-related quality of life, the subjective employment prognosis, and the number of exacerbations and sick days as secondary outcomes.

## Methods/design

### Study design and data collection

A randomized-controlled intervention study will be carried out comparing the intervention group (patient education “Asthma and Work”) with a control group (patient education “Eating behaviour”, parallel group). We estimate that in total about 180 individuals with asthma will participate in two rehabilitation clinics in Germany (Hufeland-Clinic Bad Ems: *n* ≥ 60, Clinic Bad Reichenhall: *n* ≥ 120) over a period of 15 months (recruitment, implementation, 3-month follow-up). Initially, screening for eligibility for participation takes place approximately four weeks before the start of inpatient pulmonary rehabilitation (T0). Furthermore, measurements at the beginning (T1) and at the end of rehabilitation (T2, about three weeks after T1) as well as a follow-up survey (T3, about three months after T2) are planned (see also Table 1). The data are collected primarily by using a patient questionnaire (self-reports). In addition, medical data are collected at T1 and T2 by the rehabilitation staff (physician questionnaire). The study is coordinated at the University of Duesseldorf, Germany, by the study coordinator (JS) and the study director (AL) (e.g., development of the intervention and control module, study materials, data management and statistical analysis, access to the final dataset). On-site study procedures are carried out by study assistants (e.g., recruitment, management of assignment lists of ID and contact data, documentation of drop-outs or deviations from intervention protocol, a reminder to participate at T3 by phone), and patient education is facilitated by (pre-trained) psychologists. To ensure that our study protocol reports all relevant content, we applied the SPIRITreporting guidelines [21]. The study was registered in the German Clinical Trials Registry (ID: DRKS00031843) on 17.10.2023.

**Table 1 Tab1:** Time schedule

2023					2024												2025			
Aug	Spt	Oct	Nov	Dec	Jan	Feb	Mar	Apr	May	Jun	Jul	Aug	Spt	Oct	Nov	Dec	Jan	Feb	Mar	Apr
1	2	3	4	5	6	7	8	9	10	11	12	13	14	15	16	17	18	19	20	21
Preparation intervention and control module, development of education materials																				
					Screening (T0) + recruitment															
						Pre-test^1^														
						Implementation phase (T1 + T2)														
							3-month follow-up (T3)													
							Data management and analyses													
													Paper							

^1^Month 1 of the intervention period will serve as a pre-test: There will be two rounds of feedback from the teaching psychologists to the cross-site team (approximately after 2 and 4 weeks). If necessary, adjustments to the education modules will take place afterwards

For ethical reasons, participants are informed about the general scope and contents of both patient education modules. However, a cover story (in the study information we describe a trial run of two new patient education modules to further improve rehabilitation) is intended to prevent participants from knowing which patient education represents the intervention and which the control module. This blinding can be removed at the request of the participants at the earliest after the study has been completed. The therapists who will conduct the patient educations cannot be blinded, as they will already be involved in the design of the educational modules and thus will be aware of the study content and objectives. However, it is planned that the person (JS) who will conduct the statistical analysis in the Institute for Occupational, Social and Environmental Medicine (IASUM) at the University of Duesseldorf will be blinded, i.e. the variable revealing group membership will not be made available to JS until the analysis is completed.

### Patient selection

Four weeks before rehabilitation, all patients with the primary diagnosis of asthma will be contacted by mail and asked to complete the screening questionnaire. Patients will be included in the study if they meet the following criteria (see also Table 2), which are assessed using the screening questionnaire (and partially verified by a physician questionnaire at the start of rehabilitation). All patients receive the usual rehabilitation programme, regardless of whether they take part in the study or not.

Referral diagnosis “bronchial asthma”: diagnosis before the start of the pandemic (before March 2020)^1^ + confirmation of the diagnosis (ICD-10 code J45) in the rehabilitation clinic by a pulmonologist based on clinical and lung function diagnostics with spirometry/body plethysmography at T1 (forced expiratory volume in 1 s [FEV1], FEV1/vital capacity [VC], total specific airway resistance [sR_tot_], VC, residual volume [RV]), supplemented by allergy screening (total immunoglobulin E [Ig E], specific Ig E-screening), assessment of exercise capacity (6-minute walk test) and asthmatic inflammation (fractional exhaled nitric oxide [FeNO], eosinophils/µl)Employment in an employee or civil servant relationship subject to social insurance with at least 15 h of work per week.Worked with the asthma diagnosis for at least six months.

Individuals with referral diagnosis of Chronic Obstructive Pulmonary Disease (COPD) or long/post COVID (longer-term, adverse health effects following SARS-CoV-2 infection) are excluded. Mixed leading asthma and COPD cases are accepted as long as asthma is the referral diagnosis. Similarly, individuals with additional self-reported persistent long/post COVID symptoms (e.g., fatigue) remain in the study, but– like individuals with mixed asthma-COPD– are excluded in a sensitivity analysis (see below). If all inclusion criteria are met, study participation is usually only discontinued at the participant’s request.

### Randomization

Randomization is to be performed using a random number table created with computer software (i.e., computer-assisted sequence generation). The randomization lists are created in blocks (block size varies randomly) at the IASUM (outside the clinics, central randomization) for both clinics separately (stratified randomization by study centre). Opaque, sealed envelopes numbered consecutively are sent by the IASUM to the clinics, which contain information on group membership according to the randomization list and which are to be opened in ascending order as soon as a participant is to be randomized. A study assistant at the beginning of rehabilitation will randomly assign all patients who meet the inclusion criteria and have provided informed consent to the intervention or control group. The study assistants on site (concealed allocation) do not know the size of the different blocks. This procedure is in line with current quality standards [22] and has already proven to be feasible and practicable in a large intervention study at the participating Clinic Bad Reichenhall [23].

### Sample size

We assume that over a period of 11 months, we will be able to recruit approximately 300 individuals who meet the inclusion criteria (Bad Ems: *n* ≥ 100, Bad Reichenhall: *n* ≥ 200). With a drop-out rate of 40% by T3, we can assume a sample of 180 participants (90 per group) attending at all measurement time points (Bad Ems: *n* ≥ 60, Bad Reichenhall: *n* ≥ 120). With an intermediate effect size of Cohen’s d = 0.5 [24], an alpha level of 0.05, and a statistical power of 0.8, this sample size should be sufficient to detect significant differences and the sample size is comparable to or exceeds that of similar RCTs [25–28].

### Intervention

Both groups will receive a 3-week rehabilitation program that meets the structural requirements of German healthcare insurance providers (standards for personnel, space, and medical-technical equipment) [29, 30]. The rehabilitation program includes, among other things, different non-drug therapy components such as physical training, respiratory physiotherapy, comprehensive patient education, and psychosocial counselling [31]. In addition, patients will receive a routine check-up and if necessary, the current asthma medication will be adapted according to the current guidelines (any changes to medication will be documented).

The participants of the intervention group will additionally receive the module “Asthma and Work” in a workshop with preferably about five participants each. This education module spans across 2 × 50 minutes. It offers in the first part (module A) a theoretical introduction to the topic/knowledge transfer in the form of lectures (e.g., “What is asthma self-management in general and in the workplace?” and “What does ‘job crafting’ mean?“) as well as individual and plenary exercises (peer support). In the second part (module B), the focus is on practical exercises, especially in the form of communication training and role plays (e.g., “How do I communicate specific change requests regarding my working conditions?”).

The control group, by contrast, will receive an education module addressing “Eating behaviour”. We chose this topic because eating behaviour is not part of asthma self-management behaviour. In addition to general topics of healthy nutrition (“What does a healthy diet look like? And why is a healthy diet important?”), this educational module focuses on the psychological aspects of eating (conscious and unconscious processes: Why do we eat, when and how? And how can we improve our eating behaviour?). This content is provided through lectures and exercises in individual and group work. It will have the same temporal scope (2 × 50 min) as the intervention module and will also take place in small groups and preferably in the same week of the pulmonary rehabilitation program.

At the beginning of the education module, the participants in the intervention group will receive a brochure with the education contents as well as supplementary information. Participants in the control group will receive this brochure after the 3-month follow-up. This way, the relevant education content is also made available to the control group. All participants also fill out a short and anonymous evaluation form, to be able to control the quality of the education modules from the participants’ point of view.

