The following describes the analyses in detail: Descriptive statistics, including means for continuous variables and proportions for categorical variables, will be used to summarize participant characteristics. We will determine the potential changes in primary and secondary outcomes (T1 to T2, T1 to T3) by pre-post comparisons within groups and test them for statistical significance using paired t-tests. Differences between groups (at T2 and T3) will be evaluated using univariate analyses of covariance (ANCOVAs). That is, membership in the intervention or control group will be used as the independent variable in each case, and the follow-up score of the primary outcome measures (behavioural intention, asthma self-management at work) and secondary outcome measures (self-efficacy, self-management-related knowledge, number of sick days, number of exacerbations, asthma control, asthma-related quality of life, and subjective employment prognosis) will be used as the dependent variable. Initially, only the corresponding baseline value of the primary outcome variable is included as a covariate to remove conditional bias [45, 46]. In a next step, the rehabilitation clinic [47], gender, age [48], and education [48] are additionally included as covariates. If the correlation between baseline and follow-up values is high (> 0.5), change scores are used as independent variables instead of follow-up values, as these then provide a more precise estimate [49]. For all models, the statistical model assumptions (linearity, homoscedasticity, normality of residuals) are tested. If the model assumptions are violated, appropriate analysis methods (e.g., robust regression, log transformation) are applied. In addition, to test whether comorbid COPD or long/post COVID disease affects the outcomes, sensitivity analyses will be performed excluding participants with COPD and/or long/post COVID symptoms. We will also conduct the analyses again without those who participated during the pre-test^2^, as at this point there may not yet be a routine regarding the training procedures and minor adjustments may still be made. Gender-stratified analyses are also conducted. Likewise, those with uncontrolled (ACT < 20 [32]) versus controlled asthma (ACT ≥ 20 [32]) and those with versus without a need for medical-occupational rehabilitation^3^ should additionally be analysed separately. Our primary analysis will be based on complete case analysis. In case the proportion of missing data exceeds 5% on a given variable, we will carry out sensitivity analysis employing multiple imputations.

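### Both modules are taught in groups, but the primary ANCOVA treats participants as independent; if outcomes correlate within workshops, the error rate exceeds 5%

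*Protocol article*

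**What the plan says.** Under Randomization, the unit is the individual: a study assistant "will randomly assign all patients who meet the inclusion criteria" and have consented, from lists kept separately for each clinic.

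Under Intervention, the intervention module is taught "in a workshop with preferably about five participants each", over two sessions of 50 minutes. It contains plenary exercises with peer support, communication training and role play. The control module has the same length and "will also take place in small groups"; no group size is given for it. Under Study design and data collection, "patient education is facilitated by (pre-trained) psychologists". Their number is not given, nor whether each teaches one module or both.

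Under Data analysis plan, groups are compared at T2 and T3 by univariate ANCOVA, in which "membership in the intervention or control group will be used as the independent variable in each case". The baseline value is the first covariate; clinic, gender, age and education are added next. The listed assumption checks cover linear relations, constant variance and normal residuals. Independence of observations is not among them, and neither workshop nor psychologist enters any model.

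Under Sample size, 180 completers (90 per group) are called sufficient for d = 0.5 with "an alpha level of 0.05, and a statistical power of 0.8". No ICC or design effect is mentioned.

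**The concern.** Individual randomisation makes the arms comparable at baseline, but it does not keep participants independent afterwards. People who share a facilitator, discussion and role-play partners may end up more alike than people in different workshops. Behavioural intention, the primary outcome at T2, is the kind of outcome that such sessions try to move.

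A single-level ANCOVA has no place for this shared variation. With positive within-workshop correlation it understates the standard error of the group difference, so confidence intervals are too narrow and p-values too small for both primary outcomes. Adjusting for clinic does not help, because the correlation lies between workshops within a clinic.

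**Working it through.** **Inputs from the protocol.** About 300 recruited, 40% dropout by T3, 90 completers per group, d = 0.5, alpha 0.05, power 0.80 (Sample size); about five per intervention workshop (Intervention).

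**Assumed.** A two-sided test, since sidedness is not stated. ICC 0.01 to 0.10, since none is given. Number analysed per workshop m = 5 with no loss, and m = 5 × (1 − 0.40) = 3 at T3. The same m in the control arm, whose group size is not stated.

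**1. The plan's own figure.** 300 × 0.60 = 180, so 90 per group. Under independence, the number needed per group is 2 × (1.960 + 0.842)² / 0.5² = 62.8, so 63 (126 in total). With 90 per group, power is Φ(0.5 × √(90/2) − 1.96) = Φ(1.394) = 0.918. The figure reproduces and has a margin.

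**2. Clustering in both arms.** Design effect DE = 1 + (m − 1) × ICC. Actual error of the unadjusted test = 2 × [1 − Φ(1.96 / √DE)]. Power of a cluster-adjusted analysis uses 90 / DE per group.

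| m | ICC | DE | True SE / naive SE | Actual error | Adjusted power, 90 per group |
|---|---|---|---|---|---|
| 5 | 0.01 | 1.04 | 1.02 | 5.5% | 0.908 |
| 5 | 0.05 | 1.20 | 1.095 | 7.4% | 0.865 |
| 5 | 0.10 | 1.40 | 1.183 | 9.8% | 0.809 |
| 3 | 0.01 | 1.02 | 1.01 | 5.2% | 0.913 |
| 3 | 0.05 | 1.10 | 1.049 | 6.2% | 0.892 |
| 3 | 0.10 | 1.20 | 1.095 | 7.4% | 0.865 |

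**3. Clustering in the intervention arm only.** With equal arms, the variance of the difference is inflated by the mean of the two design effects, (DE + 1) / 2.

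- m = 5: ICC 0.05 gives (1.20 + 1) / 2 = 1.10, error 6.2%; ICC 0.10 gives (1.40 + 1) / 2 = 1.20, error 7.4%.
- m = 3: ICC 0.05 gives 1.05, error 5.6%; ICC 0.10 gives 1.10, error 6.2%.

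**4. Check by simulation.** The setting was the unadjusted ANCOVA with 30 workshops of five per arm, baseline correlation 0.5, clustering in both arms and 20,000 runs per setting.

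| ICC | No dropout | 40% random dropout |
|---|---|---|
| 0 | 5.2% | 5.3% |
| 0.05 | 7.2% | 6.2% |
| 0.10 | 9.7% | 7.7% |

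These agree with the formula. With no within-workshop correlation the test holds about 5%.

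**5. Room in the sample size.** Power stays at 0.80 or more while 90 / DE is at least 63, that is, up to DE = 90 / 63 = 1.43. Every row in step 2 lies below this.

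**The case against.** The case on the other side is that the effect may be small, and several parts of it stand.

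- *The ICC is unknown.* The shared exposure is two 50-minute sessions within a three-week programme that both arms receive. The modules are preferably given in the same week, so calendar influences largely fall on both arms alike. At ICC 0.01 the error is only 5.2% to 5.5%. A reader might infer that the 5% level is certainly broken. The documents do not support that, because it depends on a correlation they do not report.
- *The control arm may not cluster.* The eating module was chosen because its topic lies outside asthma self-management, so it has less reason to make asthma outcomes alike. This roughly halves the inflation, as step 3 shows.
- *Groups may be smaller than five.* A reader might take five as the size in both arms, but it is stated for the intervention only, and as a preference. At the smaller clinic, 11 months is about 48 weeks or 16 three-week stays. A hundred recruits give about 6 per stay, or 3 per arm. The rows for m = 5 may therefore be too high for about a third of the sample.
- *Power is adequate.* A reader might infer that the trial is too small. It is not, for the ICCs considered here.

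It could also be said that this belongs in a statistical analysis plan. That carries less weight: the article fixes the model, its covariates and its assumption checks, and a plan that followed them would carry the omission forward. In the other direction, correlation at psychologist level could add to the inflation, since each psychologist may teach many participants. The protocol does not give the figures needed to size this.

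**Conclusion.** The point holds in conditional form. The stated primary model ignores the grouping that the delivery of both modules creates, and any positive within-workshop correlation makes its standard errors too small. For an ICC of 0.01 to 0.10 in both arms, the actual two-sided error is about 5.5% to 9.8% with five analysed per workshop and 5.2% to 7.4% with three. If only the intervention arm clusters, the figures for ICC 0.05 to 0.10 fall to about 6.2% to 7.4% and 5.6% to 6.2%. The direction does not depend on the ICC chosen; the size does. The defect concerns the validity of intervals and p-values for both primary outcomes. The Sample size section can stay as it is.

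**What to change.** - Record a workshop ID and a psychologist ID for every participant in both arms at the time of delivery. Code them neutrally, so that they do not tell the blinded analyst which arm is which.
- Fit the primary models with a random intercept for workshop, its variance allowed to differ by arm, and small-sample degrees of freedom. Alternatively, keep the ANCOVA and use standard errors clustered on workshop with a small-sample correction. Choose one of the two before the data are seen.
- Keep clinic as a covariate.
- For the intention-to-treat analysis, enter participants who attended no session under the workshop for which they were scheduled.
- Examine psychologist effects in a sensitivity analysis.

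The cost is two ID variables, slightly wider intervals and a little more analysis work. No extra participants are needed. If the within-workshop correlation turns out near zero, the adjusted analysis loses almost nothing.
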